### Sample

We aim to recruit a sample of 232 participants, that is, 116 per group. The PLHIV who will participate in the study must be at least 18 years of age and on ART for at least 6 months. The reason for the latter criterion is that we wish the therapy-management intervention to focus on adherence over time rather than on treatment initiation. Internet access is another inclusion criterion. This will introduce a selection bias in the study; however, the bias will be offset by the inherent value in evaluating an innovative service-delivery method that, in the near future, could reach a vast number of people at low cost and, thus, constitute an important option for providing follow-up to groups with a chronic health problem. In this study, both the experimental group and the control group will be composed of PLHIV with similar characteristics, who have internet access and who use it to obtain information relative to their health condition.

The sample size was estimated based on the studies by Tuldrà *et al.*[84] and Pradier *et al*. [18] carried out with PLHIV, and on the systematic review by Haynes *et al*.

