[24] of adherence-related interventions intended for various groups. In the study by Tuldrà *et al*. [84], there was a difference of 25 percentage points between the control group and the experimental group in terms of treatment adherence (69% vs. 94%, respectively). For Pradier *et al.*[18], the proportion of treatment-adherent participants was 58% in the experimental group and 63% in the control group at the start of the study, and 75% and 60% respectively after the intervention. We calculated our sample size on the assumption that the proposed intervention (the web application) will increase the percentage of treatment-adherent participants in the experimental group by 20%. The percentage of treatment-adherent participants at the start of the study will be the same as that reported by Godin *et al*. [78] (that is, 50%), given that our recruitment pool is very similar to theirs. This is a conservative assumption given that the variance in the difference between the two proportions will be larger, with the benchmark proportion set at about 50%. Consequently, the sample size required to detect a difference of 20% (50% treatment-adherent participants in the control group versus 70% in the experimental group) will be larger than for other scenarios with the same 20-point difference. Hence, to detect a difference of 20 percentage points at 80% power and a χ^2^ test two-tailed α value of 0.05, the required sample size is 186 participants, that is, 93 per group. As we are assuming a 20% attrition rate (that is, the same rate seen in the studies by Goujard *et al*. [14] and Tuldrà *et al.*[84]), the sample size has been set at 232 participants. With a sample of 186 participants completing the study, the statistical power will be enough to detect a moderate effect on the intermediate variables. In particular, with *n* = 186, an α value of 0.05 (two-tailed Student’s *t*-test) will allow detection of the difference between the two percentages, corresponding to a standard deviation of 50% and power of greater than 90%.

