### Type of analysis used

To establish whether the experimental and control groups are equivalent, the means and medians of the continuous variables and the frequency distributions of the discrete variables will be compared using descriptive analyses. The principal analyses will focus on comparing the two groups in terms of treatment adherence (the study’s main outcome, considered as a binary variable with adherent being ≥ 95% and non-adherent > 95%) at the end of follow-up at T6. An intention-to-treat (ITT) analysis will be carried out to evaluate the true value of the intervention in a real context. Consequently, in the following analyses, all participants will be assessed in their respective randomization group as to whether they are following the procedure or have been lost to attrition during follow-up. In accordance with the principles of ITT, participants who drop out and those for whom there is no adherence measure at T6 will be considered as non-adherent.

The primary hypothesis is that the VIH-TAVIE intervention will increase the proportion of treatment-adherent patients at T6. This hypothesis will be tested using a χ^2^ test with 1 degree of freedom. If preliminary analyses show that the two groups differ on certain characteristics, multivariate logistic regression will be used to adjust the intervention’s effect on these characteristics, which will be considered as potential confounding variables. In this case, the two-tailed Wald’s test will be used to test the intervention’s adjusted effect.

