As emphasized by Bull *et al*. [94], online longitudinal evaluations entail following up participants and completing various measures. According to Bull *et al.*[94] and Bennett and Glasgow [92], online studies have a lower retention rate than that of traditional studies, and attrition rates of 40% are not uncommon. However, Schubart *et al.*[102] and Bull *et al*. [103] highlighted a number of elements that foster a high retention rate in online studies, including the availability of a health professional to provide feedback, the dynamic qualities of the study website, and the inclusion of a clinician coach, such as a nurse, in the intervention. All of these will be considered in this study.

For the purpose of encouraging participants to continue with the study, reminder e-mails (maximum of three to four) will be sent out at 7-day intervals prior to measurement. Bull and colleagues [94] noted that e-mails alone were not sufficient to communicate with participants, and that a variety of communication modes should be used. They suggested that participants should be asked to provide other contact details such as home and mobile telephone numbers, and a home address. According to these authors, a balance must be struck between guaranteeing confidentiality and ensuring follow-up. Because the technology we plan to use is complex and can present many problems and bugs, we plan to assign a resource person (technical support) to help users in this regard. According to Paul and colleagues [101], this constitutes a key source of support if the research budget allows it.

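### The stated 80% power is for an analysis of completers; with dropouts scored non-adherent, as the primary analysis requires, 232 participants give about 69% at the assumed 20% attrition and about 48% at 40%

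*Protocol article*

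**What the plan says.** **Sample size (Sample).** The aim is "to detect a difference of 20 percentage points at 80% power", and the planning rates are "50% treatment-adherent participants in the control group versus 70% in the experimental group". For a χ² "test two-tailed α value of 0.05, the required sample size is 186 participants, that is, 93 per group". The section continues "As we are assuming a 20% attrition rate" and sets the total at 232; at its start it gives the target as "We aim to recruit a sample of 232 participants, that is, 116 per group". It then speaks of the 186 as those who finish the study.

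**Primary analysis (Type of analysis used).** The main hypothesis is tested at T6 by a χ² "test with 1 degree of freedom". Everyone is analysed in the group to which they were randomized, including those lost to follow-up, and "participants who drop out and those for whom there is no adherence measure at T6 will be considered as non-adherent".

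**Attrition (Challenges of an online randomized controlled trial).** The article reports that online studies retain fewer participants than traditional ones and that "attrition rates of 40% are not uncommon". It then lists features that help retention and says that the study will consider them. Under Recruitment and online data collection, the whole trial is to be run online.

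**The concern.** The sample size and the primary analysis treat the same dropouts differently. Dividing by 0.8 assumes that 20% of participants vanish from both numerator and denominator and that the 20-point contrast among the rest is untouched. The analysis rule leaves them in the denominator and counts them as failures in both groups, which shrinks the contrast in proportion to the attrition. Having 116 rather than 93 per group in the test does not make up for that shrinkage.

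If so, the trial does not have the power it states. A real 20-point benefit would be missed more often than the planned one time in five, and a null result would be judged against a sensitivity that the design lacks. The gap widens if retention is nearer to the level the article itself reports for online studies.

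**Working it through.** **Inputs, all from the article.** Control 50%, experimental 70%, two-sided α 0.05, power 80%, 20% attrition, 116 per group (Sample); χ² test on all randomized, missing T6 adherence scored non-adherent (Type of analysis used); 40% as a cited attrition rate (Challenges of an online randomized controlled trial).

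**Formulas.** Two proportions p₁ and p₂, pooled variance under the null, no continuity correction, p̄ = (p₁ + p₂)/2:

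- n per group = [1.96·√(2p̄(1−p̄)) + 0.8416·√(p₁(1−p₁) + p₂(1−p₂))]² / (p₂ − p₁)²
- power = Φ(z), with z = [(p₂ − p₁) − 1.96·√(2p̄(1−p̄)/n)] / √[(p₁(1−p₁) + p₂(1−p₂))/n]

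**Step 1: the article's own figure.** With 0.50 and 0.70, n = 93.0 per group, 186 in total, and power at n = 93 is 80.0%. Then 186/0.8 = 232.5, which matches the stated 232. The calculation reproduces, so this is the method used.

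**Step 2: the planned primary analysis at 20% attrition.** If a fraction d is lost in each group and scored non-adherent, each proportion is multiplied by (1 − d):

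- control: 0.8 × 0.50 = 0.40
- experimental: 0.8 × 0.70 = 0.56
- contrast: 0.16, p̄ = 0.48, n = 116
- z = [0.16 − 1.96·√(2 × 0.48 × 0.52/116)] / √[(0.24 + 0.2464)/116] = (0.16 − 1.96 × 0.0656)/0.0648 = 0.485
- power = Φ(0.485) = 68.6%

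**Step 3: over a range of attrition, 116 randomized per group.** The last column shows an analysis that simply drops the missing, for comparison.

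| Attrition in each group | Proportions tested | Contrast (points) | Power, missing = non-adherent | Power, completers only |
|---|---|---|---|---|
| 10% | 45% vs 63% | 18 | 78.9% | 84.4% |
| 20% | 40% vs 56% | 16 | 68.6% | 79.9% |
| 30% | 35% vs 49% | 14 | 58.0% | 74.4% |
| 40% | 30% vs 42% | 12 | 47.7% | 67.7% |

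**Step 4: what 80% would take under the planned rule.** The n formula gives 152 per group (304 in total) at 20% attrition and 250 per group (500) at 40%. Put the other way, with 116 per group and 20% attrition, 80% power is reached at about 50% vs 73% among those measured: 0.40 vs 0.584 gives 80.4%.

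**Step 5: does the approximation matter?** Exact binomial enumeration of the uncorrected χ² test gives 79.9% for the article's case (93 per group), 70.6% for 40% vs 56% and 47.6% for 30% vs 42%. With unpooled variance the last two are 69.5% and 48.4%. The result does not depend on the formula.

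**Step 6: unequal attrition.** With 20% lost in control and 25% in experimental, the test compares 40% with 52.5% and power is 48%. With 25% and 20%, it compares 37.5% with 56% and power is 81%.

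**The case against.** The strongest reply is that 69% depends on what 50% and 70% mean. The 50% is introduced as adherence at the start of the study, so it could be a rate for everyone randomized. Dropouts may also be less adherent than those who stay, which would make scoring them non-adherent closer to the truth. If 50% and 70% are true rates in all randomized participants, with 20% attrition in each group, the power depends on how adherent the dropouts are relative to their whole group. It is 69% if equally adherent, 74% if three quarters as adherent, 79% if half as adherent and 88% if none are.

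This is a fair sensitivity range, but it is not the calculation in the article. Had the rates already counted dropouts as failures, no inflation would have been needed. The 88% case also implies adherence of 0.50/0.8 = 62.5% and 0.70/0.8 = 87.5% among completers, which the article nowhere assumes. The article applies 50% and 70% to 186 people who finish, and on that reading the unseen adherence of dropouts does not enter the test.

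Three further points:

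- *Equal attrition is an assumption.* True. The article plans with one rate and no difference between groups. Step 6 shows how sensitive the test is. Where unequal loss raises the power, part of the apparent effect is differential dropout rather than adherence.
- *40% is background, not the planning rate.* This stands. The article follows it with retention measures, and it also plans reminders, technical support and gift certificates. So 48% belongs at the end of a range, and the main figure is the one at the article's own 20%.
- *No sum is wrong, and type I error is unaffected.* Also true: 93, 186 and 232 are correct for a completers analysis, and with no effect and equal attrition the test keeps its level. The fault is that the stated power belongs to a different analysis.

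**Conclusion.** The concern holds. Under the primary analysis as written, 232 participants give about 69% power at the planned 20% attrition, not 80%. The chance of missing a true 20-point benefit is then about 31% rather than 20%. If attrition reached 40%, it would be about 52%.

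These figures rest on two assumptions: attrition is equal in the two groups, and 50% and 70% are the rates among participants with a T6 measure. The second follows from the article's inflation step. The first follows its single attrition rate, but modest departures move the power a long way in either direction. The article states both the power and the missing-data rule, so this is a conflict within the document and not a detail left to another one.

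**What to change.** In the Sample section, replace the power statement with one for the analysis actually planned: 40% vs 56% with 116 per group, about 69% power at 20% attrition in each group. Add the range (79% at 10%, 58% at 30%, 48% at 40%), state the two assumptions, and show at least one case of unequal attrition.

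Alternatively, keep the 80% statement and make the primary analysis one that it describes, meaning an analysis of T6 adherence in which missing values are not automatically failures. Scoring the missing as non-adherent would then become a sensitivity analysis. The completers figures apply approximately: about 80% at 20% attrition and 68% at 40%, so a range should be shown here too. Because data collection has begun, such a change should be made and dated before anyone sees outcomes by group.

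The first option costs wording only, plus a less favourable stated figure. Neither option needs more participants.

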### Experimental conditions

The virtual intervention consists of four computer sessions of 20 to 30 minutes in length. There will be a 1-week interval between sessions to ensure the progressive acquisition and consolidation of skills, thus, access will be controlled and pre-determined within this interval. It will be possible at all times for participants to revisit previous sessions. Access will be unlimited in terms of intensity, frequency, and time of use throughout the duration of the study. Delivering an intervention by computer affords a key advantage in that it allows complete control of the content. Moreover, the intervention’s parameters are recorded, thus making it possible to obtain a reliable picture of the actual intensity, duration, and frequency of the intervention. These data will be available for subsequent analyses.

### Control group

Participants in the control group will be invited to consult, at their convenience and from the location of their choice, a list of pre-determined websites offering information on antiretroviral medications, their side-effects, and their interactions.

### Measurement

Adherence will constitute the principal outcome, and for the purposes of the study, it will be evaluated through a self-administered questionnaire that was developed for and validated on the target population in accordance with recommendations relative to the measure of treatment adherence [85]. The questionnaire comprises seven items that serve to determine how many times a person forgets to take their medication. The questionnaire is designed to place the respondent in a context where events and situations could lead to lapses. The questionnaire’s validity was assessed (sensitivity 71%; specificity 72%; correct classification 72%; odds ratio 6.15) using immunologic (CD4 count) and virologic (viral load) parameters as validation criteria. Adherence was defined as the intake of at least 95% of the prescribed tablets. Although there is no clear minimum cut-off point defining what constitutes sufficient ART adherence for achieving optimal treatment efficiency [5], this is generally set at between 90% and 95% [86]. Self-reported viral load and CD4 counts will also be recorded.

The intermediary measures will be assessed by means of validated instruments. Self-efficacy regarding medication intake will be measured using 12 items rated on a 5-point Likert scale (here is an example of an item: “I can take my antiretroviral medications even if I’m in the company of people who don’t know I’m seropositive”). These items are adapted from a scale developed by Godin *et al*. [78] and have previously been used on a large sample (*n* = 399). To adapt the instrument to our context (that is, antiretroviral medication intake), the items have been reformulated by expert consensus following the results of a focus group and of a literature review, and on the basis of Bandura’s theoretical model of self-efficacy. A content validation has also been carried out.

Attitude toward medication intake will be evaluated through six items rated on a five-point Likert scale. These items emerged from focus groups of PLHIV who were on treatment. A preliminary version of the instrument was tested on 35 PLHIV. The scale was previously used on a large sample (*n* = 399) [78], obtaining a Cronbach’s α coefficient of 0.83 and a test-retest reliability coefficient of 0.72.

Symptom-related discomfort will be measured using the Self-Completed HIV Symptom Index [87]. This 20-item instrument determines using a scale of 1 to 4 whether symptoms are present (0 = absence) and the degree of discomfort experienced. The instrument has been validated on 188 PLHIV, and it was found to have acceptable psychometric properties, including good construct validity.

Social support will be evaluated using the Medical Outcome Survey [88,89]. One dimension of social support will be measured by subscale of emotional support, which has eight item, each of which is rated on a five-point Likert scale. The instrument has been found to have good content validity and appreciable internal consistency.

A sociodemographic questionnaire will cover personal characteristics such as sex, age, family situation, level of education, employment situation, number of children, and questions about HIV, the therapeutic regimen, and presence of symptoms.

### Recruitment and online data collection

The study will be conducted entirely online. The project will be advertised on the websites of resources available to PLHIV, where a hyperlink and a banner will be inserted to redirect parties interested in participating in the online research. The targeted resources include partner clinics, community agencies, and other organizations that deliver teaching, care, treatment, or follow-up to PLHIV. In addition, health professionals and stakeholders will be invited to inform their PLHIV about the study. To promote the project among PLHIV, different communication strategies will be used: 1) traditional methods, such as poster and information brochures; and 2) technological or virtual methods, by advertising the study on websites of organizations (medical clinics, association for PLHIV) that are often visited by PLHIV.

Individuals who will visit the study’s website will view a short video clip of testimonials by a few PLHIV, then they will be given information on the study. After accepting the conditions of the study and consenting to take part in it, they will sign up for the study by providing an email address and a pseudonym. Each participant will be validated through an email address check. Once this step is completed, a hyperlink will be emailed to allow participants to access the first questionnaire online on the website, and only after having completing this questionnaire will they be randomly assigned by the computer system to the experimental group or the control group. Participants in the control group will be invited to consult pre-determined websites that offer information on ART and its associated side-effects. Participants in the experimental group will be offered the virtual intervention through the web application. At 3 and 6 months after the initial measurement, participants will complete the online questionnaires again. A reminder to this effect will be emailed to them in the days prior to the scheduled measurement. Participants will be compensated for their time spent on the study with a gift certificate for each measurement time completed.

### Type of analysis used

To establish whether the experimental and control groups are equivalent, the means and medians of the continuous variables and the frequency distributions of the discrete variables will be compared using descriptive analyses. The principal analyses will focus on comparing the two groups in terms of treatment adherence (the study’s main outcome, considered as a binary variable with adherent being ≥ 95% and non-adherent > 95%) at the end of follow-up at T6. An intention-to-treat (ITT) analysis will be carried out to evaluate the true value of the intervention in a real context. Consequently, in the following analyses, all participants will be assessed in their respective randomization group as to whether they are following the procedure or have been lost to attrition during follow-up. In accordance with the principles of ITT, participants who drop out and those for whom there is no adherence measure at T6 will be considered as non-adherent.

The primary hypothesis is that the VIH-TAVIE intervention will increase the proportion of treatment-adherent patients at T6. This hypothesis will be tested using a χ^2^ test with 1 degree of freedom. If preliminary analyses show that the two groups differ on certain characteristics, multivariate logistic regression will be used to adjust the intervention’s effect on these characteristics, which will be considered as potential confounding variables. In this case, the two-tailed Wald’s test will be used to test the intervention’s adjusted effect.

For the secondary analyses, the two groups will be compared on all the repeated measures of adherence (T3 to T6) using a generalized estimating equation (GEE) approach that generalizes the logistic regression for longitudinal data with repeated measures of the binary measure [90]. We will assume that the covariance matrix has an auto-regressive structure of order = 1 to account for inter-correlations between repeated measures (over the course of follow-up) with the same participants. The difference between repeated measures of adherence (T3 and T6) will constitute the binary dependent variable. The binary intervention indicator, the indicator of time since the follow-ups (3 and 6 months) and, if necessary, the confounding variables, will be included as independent variables. Finally, the interaction between the intervention effect and the time effect will be added to the GEE model and will be tested to verify whether the intervention’s effect on adherence varies over time. In the GEE analyses, a conservative approach will be used and, accordingly, all missing data for the dependent variable (adherence) will be replaced with ‘non-adherent’. The same approach will be used to evaluate the effects of the intervention on the repeated measures of the intermediary variables. However, given that these variables will be measured by means of quantitative scales, a linear mixed model for repeated measures of a continuous dependent variable [91] will be used instead of the GEE model.

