## Design

We opted for an online randomized controlled trial (RCT) to evaluate the efficacy of the virtual intervention (web application) primarily in influencing ART adherence. Adherence is a behavioral indicator that can be predicted in part by cognitive and affective variables, particularly sense of self-efficacy and attitude towards antiretroviral medication intake [78]. These variables are in turn explained by perceived social support, relationship with health professionals, and absence of adverse effects. These intermediate variables, which are the targets of our intervention, will allow effective change in the short term. They constitute mediators capable of explaining the intervention’s effect on adherence. There will be three measurement times: baseline (T0), after 3 (T3) and 6 months (T6) of baseline measurement. Participants will be drawn from a convenience sample and will be randomly assigned either to an experimental group that will use our web application, or to a control group that will be presented with a list of various websites of interest.

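### T0 adherence is known for everyone at randomisation, but it can enter the primary analysis only through an undefined, data-driven adjustment clause

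*Protocol article*

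**What the plan says.** All of this is in the Protocol article.

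- **Timing of T0** (Recruitment and online data collection). Participants complete the first questionnaire, and "only after having completing this questionnaire will they be randomly assigned by the computer system to the experimental group or the control group". T0 is therefore available for everyone randomised.
- **Primary test** (Type of analysis used). For binary adherence at T6: "This hypothesis will be tested using a χ^2^ test with 1 degree of freedom".
- **Conditional adjustment** (same section). "If preliminary analyses show that the two groups differ on certain characteristics, multivariate logistic regression will be used to adjust the intervention’s effect". The next sentence changes the test: "In this case, the two-tailed Wald’s test will be used to test the intervention’s adjusted effect".
- **Longitudinal analysis** (same section). "the two groups will be compared on all the repeated measures of adherence (T3 to T6) using a generalized estimating equation (GEE) approach". The model holds arm and time; confounders are added only where this is judged necessary.
- **Missing T6 adherence** (same section) is counted as non-adherent, and everyone is analysed as randomised.
- **Sample size** (Sample). 50% versus 70% adherent, 80% power, two-sided 5% chi-square: 93 per group, raised to 232 in total for 20% attrition.

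**The concern.** The baseline value of the outcome is usually the first candidate for adjustment, and here it is complete by design. The plan leaves it out by default and lets it in only if the groups are seen to differ.

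That clause has three weaknesses. It does not say which characteristics count. It does not say how large a difference counts; the baseline comparison itself is described only as descriptive. And it moves the primary hypothesis from a chi-square test to a Wald test according to what is observed, so two analysts following the text could report different primary p-values.

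It also misses the point of adjustment. Most of the benefit of a prognostic covariate comes from explaining outcome variation in every trial, including those where the arms look balanced. A rule that acts only on visible imbalance leaves most of that benefit unused.

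**Working it through.** **1. The plan's own figure.** Inputs from Sample: 0.50 v 0.70, two-sided 0.05, power 0.80; pooled proportion 0.60.

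n = [1.96·√(2·0.6·0.4) + 0.8416·√(0.25 + 0.21)]² / 0.20² = (1.3579 + 0.5708)² / 0.04 = 93 per group, 186 in total. Then 186/0.8 = 232.5, against the stated 232. The plan's figure reproduces, and it is for the unadjusted test.

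**2. Power of the unadjusted test.**

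- 93 completers per arm: SE under the null √(0.6·0.4·2/93) = 0.0718; SE under the alternative √(0.46/93) = 0.0703; Φ[(0.20 − 1.96·0.0718)/0.0703] = 80.0%.
- Plan's missing-data rule, 116 per arm, 20% random dropout in both arms: the rates become 0.8·0.50 = 0.40 and 0.8·0.70 = 0.56. SEs are 0.0656 and 0.0648; Φ[(0.16 − 1.96·0.0656)/0.0648] = 68.6%. Simulation gives about 70-71%. Summing Bin(x; 116, 0.40)·Bin(y; 116, 0.56) over all tables with |z| > 1.96 gives 70.6%, so the gap from 68.6% is approximation error. I use about 71%.

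**3. Power with T0 adherence always in the model.** Assumptions: 50% adherent at T0 (Sample) and a T0-T6 correlation φ of 0.2 to 0.6, which the documents do not give. As a rough guide, adjustment multiplies the SE by √(1 − φ²). For φ = 0.4 at 93 per arm the factor is 0.917, and Φ[(0.20 − 1.96·0.0658)/0.0645] = 86.4%.

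Simulated power of the adjusted analysis, under two ways of building the data (a common odds ratio across T0 strata / the same φ in both arms):

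| φ | 93 completers per arm (unadjusted 80%) | 116 per arm, missing = non-adherent (unadjusted about 71%) |
|---|---|---|
| 0.2 | 81% / 81% | 70% / 70% |
| 0.3 | 83% / 83% | 71% / 71% |
| 0.4 | 85% / 87% | 73% / 73% |
| 0.5 | 89% / 90% | 75% / 76% |
| 0.6 | 92% / 94% | 78% / 79% |

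The gain shrinks in the last column because dropouts scored as failures carry no information about T0. If dropout is unrelated to T0, φ is multiplied by 0.8·0.5/√(0.4·0.6) = 0.82 in the control arm and by 0.8·√0.21/√(0.56·0.44) = 0.74 in the experimental arm. A φ of 0.5 thus becomes about 0.41 and 0.37.

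At φ = 0 under the missing-data rule, simulated power was 70.4% for the chi-square and 68.9% adjusted. The worst-case cost is about 1-2 points.

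**4. Power with the plan's conditional clause.** The plan gives no trigger, so I assume adjustment when T0 adherence differs at p<0.05.

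| φ | 93 per arm: chi-square → conditional | 116 per arm, missing rule: chi-square → conditional |
|---|---|---|
| 0.2 | 79.6% → 79.6% | 70.3% → 70.3% |
| 0.3 | 79.2% → 79.6% | 70.5% → 70.5% |
| 0.4 | 80.5% → 81.1% | 71.0% → 71.2% |
| 0.5 | 79.6% → 80.8% | 71.2% → 71.4% |

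That is a gain of 0 to about 1 point. Type I error by this route stayed at about 5% or below.

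**5. Imbalance that the trigger would miss.** With 116 per arm and 50% adherent, the SE of the T0 difference is √(0.25·2/116) = 6.6 points, so p<0.05 needs a gap of about 1.96·6.6 = 12.9 points. A gap of 10 points or more arises by chance about 13% of the time. At φ = 0.5, a 10-point gap moves the T6 contrast among completers by about 0.5·10 = 5 points, a quarter of the 20-point target, and would not trigger adjustment.

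**The case against.** The strongest reply is that the plan does provide for adjustment. A reader of the chi-square sentence alone might infer that T0 adherence is shut out of the analysis. It is not: the next sentences, and the matching provision for the GEE, let it in if the groups differ. That stands, and it is why the criticism is of how the route is built. A large visible T0 imbalance would probably be dealt with.

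Nor is anything invalid. An unadjusted chi-square is a sound randomised comparison and matches the sample-size calculation. A reader might infer that a data-dependent switch inflates the type I error; under a fixed p<0.05 trigger the simulations show no such inflation.

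The size of the gain is also open to challenge. The completer figures are for an analysis the plan does not use, since it counts everyone randomised and scores missing as failure. On that basis nothing is gained at a correlation of 0.3 or below. No passage says how well T0 predicts T6; an adherence rate near 50% at the start does not settle it. The 0.72 reported for the attitude scale is a test-retest coefficient and cannot serve as a T0-T6 correlation.

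Finally, it is tempting to say that T0 is also left out of the mixed models for the intermediate scales. The article does not say so. The Hypotheses section lists those measures at T0, T3 and T6, and the analysis section leaves the role of T0 unstated, which a condensed article may do.

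What survives is that the adherence analyses are described in detail, down to the test, its degrees of freedom and the Wald alternative. The conditional clause is therefore a stated choice, and a poor one.

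**Conclusion.** The point holds as a worthwhile improvement and not as an error that invalidates the trial. The plan has a complete baseline measure of its primary outcome, uses it only if an unspecified imbalance appears, and so leaves the primary test open.

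Fixed adjustment would be worth about 1 to 12 points of power among completers, and about −1 to +7 points under the plan's own missing-data rule, for assumed correlations of 0.2 to 0.6 with a common odds ratio. The gain under that rule becomes visible only from about 0.4 upwards. These figures also assume 20% dropout, equal in both arms and unrelated to T0.

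A reader might infer that adjustment would bring the trial back to its planned 80%. It would not: the fall to about 71% comes from scoring missing outcomes as non-adherent, and even at a correlation of 0.6 adjusted power is only about 78-79%. That loss is a separate matter.

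**What to change.** - Replace the conditional clause with one prespecified primary model: logistic regression of T6 adherence on arm and T0 adherence, in all randomised participants, with the two-sided 5% test of the arm term as the primary test.
- Report a standardised (marginal) risk difference with 95% CI beside the odds ratio. The adjusted odds ratio is conditional on T0, whereas the hypothesis and the sample size are framed as a difference in proportions.
- Keep the unadjusted chi-square as a supportive analysis.
- Put T0 adherence in the GEE as a fixed covariate, whatever the observed balance.
- Keep the baseline comparison descriptive, with no influence on the choice of model. Any further covariates should be named in advance.

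The cost is wording only, since the data are already collected. Data collection has begun (Trial status), so the change should be dated and made before outcomes are examined by group. The downside is a loss of about 1-2 points of power if T0 turns out to predict T6 weakly.
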